#### Primary outcome

The primary outcome (OAS-M) at the various follow-up times will be analysed using a hierarchical mixed-effects linear regression with baseline OAS-M, length of sentence for index offence, and the stratification factors used in the randomization (except for site) as fixed effects. Patient ID and site will be included as random effects. A treatment effect parameter for each follow-up time will be included, although the primary one of interest will be treatment effect at 12 months. Two-sided *p* values less than 0.05 will be classed as significant.

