### Sample size and power calculation

The sample size (*N* = 302) has been chosen to have 90% power, at a two-sided 5% significance level, to detect a significant difference between groups when the change in OAS-M score is on average 10 points less in the MBT arm (with a standard deviation of 20) at the primary endpoint 12 months after randomization. Hollander et al. [68] reported the pooled standard deviation of the change in OAS-M score from baseline to 10-week follow-up as being just over 9 for the pharmaceutical intervention assessed in that study. Due to the longer follow-up period of the present trial and the non-pharmaceutical nature of the planned intervention, we have chosen to increase the standard deviation used in our power calculation to 20. To take into account potential clustering by clinician in the MBT arm, we assume the intraclass correlation coefficient to be 0.05. In this case, using established methods to take account of clustering [69], 95 participants per arm will give 90% power. We anticipate attrition and dropout to be 37%, based on several sources including our own preliminary work and several larger data sources (a meta-analysis of attrition rate in offender treatment literature [70], a systematic review of non-completion of treatment for personality disorder [71], and an empirical evaluation of treatment disengagement in offenders with personality disorder [72]). To account for this loss, initial recruitment of 151 participants per arm is anticipated to result in 95 participants remaining per arm after attrition and dropout. Our target sample size is therefore 302 participants, which will give sufficient power to detect a medium effect size of 0.5 change in participants’ OAS-M score.

Demographic and clinical details from those refusing randomization will be retained to explore whether the trial population is representative. To assess treatment acceptability, we will compute the proportion of referred individuals who never attended, the number of sessions attended, and the number who drop out of treatment or request to be referred to other treatments. All participants who do not formally withdraw from the study will be followed up on routine measures of outcome.

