#### PAU supplemented with MBT-ASPD

The treatment intervention is a 1-year programme of group and individual sessions of MBT-ASPD. Participants randomized to MBT-ASPD receive weekly group therapy for 75 min and monthly individual therapy for 50 min. Each MBT-ASPD group is run by two trained MBT clinicians and contains a maximum of eight participants, using an ‘open’ rolling entry group, with new participants joining as others leave. The group process enables participants to challenge each other about their understanding of current self-identified critical interpersonal experiences and focuses particularly on elaborating the mental state background of interactions characterized by conflict that might normally trigger aggression. The content of the group therapy sessions is steered by the clinicians toward encouraging the participants to talk about their mental states related to recent violent incidents by linking their actions to a broader range of their current subjective and emotional experience (i.e. to ‘mentalize’ them). A monthly 50-min individual session provides an opportunity for participants to address personal issues that have occurred in the group. Many participants find it more difficult to talk in front of other members of the group about the relationship difficulties they experience in their external lives, and may use the individual sessions to do this too. Both group and individual sessions focus on identifying thoughts and feelings associated with aggressive impulses, with particular emphasis on understanding emotional cues, recognizing emotions in oneself and others, understanding others’ experiences in relation to one’s own, and clarifying threats of loss to mentalizing in the context of life experiences, both currently and historically.

All participants randomized to this arm of the study have an allocated clinician. Staff providing MBT sessions are chartered health professionals with a core clinical training background (e.g. clinical psychology, nursing, medicine) who have undergone an MBT training course. Where possible, recently trained clinicians are paired with an experienced clinician to provide group MBT.

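### The primary model omits the MBT-arm clinician clustering that the sample size assumes; if that clustering exists, type I error is about 6.5% rather than 5%

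*Protocol article*

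**What the plan says.** The article makes three statements that bear on this point.

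- *Sample size and power calculation.* The trial is sized for "90% power, at a two-sided 5% significance level", for a 10-point difference with a standard deviation of 20. On clustering it says: "To take into account potential clustering by clinician in the MBT arm, we assume the intraclass correlation coefficient to be 0.05". The result is that "using established methods to take account of clustering [69], 95 participants per arm will give 90% power". After 37% attrition this becomes 151 per arm, 302 in total.
- *PAU supplemented with MBT-ASPD.* "Each MBT-ASPD group is run by two trained MBT clinicians and contains a maximum of eight participants". Entry to groups is rolling, and each MBT participant has an allocated clinician. Nothing corresponding exists in the PAU arm.
- *Statistical analysis, Primary outcome.* The model for OAS-M has fixed effects for baseline score, sentence length and the stratification factors other than site. "Patient ID and site will be included as random effects". The contrast of interest is the treatment effect at 12 months, judged at two-sided p < 0.05.

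No clinician term, group term, site-by-treatment term or robust variance is mentioned anywhere in the article.

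**The concern.** This is a partially nested design: individuals are randomized, but participants in one arm share clinicians and those in the other do not. The sample size section recognises this; the primary model does not.

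The two random effects that are named do not fill the gap. The site intercept is common to both arms, and randomization is individual, 1:1 and minimized by site, so it largely cancels when MBT is compared with PAU within a site. The patient intercept treats patients as independent of each other, so it absorbs clinician variance as if it were patient variance. The model then gets the total variance about right and the correlation among MBT participants wrong.

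The consequence, if MBT outcomes do cluster by clinician, is a reported standard error that is too small for the primary contrast, an interval that is too narrow, and a test that rejects a true null more often than 5%. The trial would have recruited extra participants to pay for clustering and then tested as though there were none. Because the article lists the random effects explicitly, this is an inconsistency between two stated choices and not a detail left open for the SAP.

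**Working it through.** **Inputs from the article.** Two-sided alpha 5%, power 90%, difference 10, SD 20, ICC 0.05 in the MBT arm only, 95 analysed per arm, attrition 37%, 13 sites.

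**Input not in the article.** The number of participants per clinician, m. It is back-solved below and then varied.

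**1. Reproduce the plan's figures.**

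Without clustering: n = 2 × (1.96 + 1.2816)² × (20/10)² = 84.1, so 85 per arm (86 with a t-based calculation).

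With clustering in the MBT arm only: n = (1.96 + 1.2816)² × (20/10)² × (DE + 1), where DE = 1 + (m − 1) × 0.05.

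Setting n = 95 gives 42.03 × (DE + 1) = 95, so DE ≈ 1.26 and m ≈ 6.2. Cluster sizes of 5, 6 and 7 give 92.5, 94.6 and 96.7.

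Attrition: 95 / 0.63 = 150.8, so 151 per arm and 302 in total. The plan's figures reproduce.

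**2. Standard error and type I error when the clustering is left out.**

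With n per arm, the true variance of the contrast is proportional to (DE + 1)/n. The model without a clinician term works with 2/n. So

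- SE ratio = √[(DE + 1)/2]
- type I error = 2 × [1 − Φ(1.96 / SE ratio)]

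At m = 6.2: SE ratio = √(2.26/2) = 1.063, and 1.96/1.063 = 1.844, which gives 6.5%. The reported standard error is 1/1.063 = 0.94 of the true one, about 6% too small.

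**3. Range over the unstated cluster size, ICC 0.05.**

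| m | How it arises | SE ratio | Type I error |
|---|---|---|---|
| 3.7 | 95 over 13 sites, two clinicians each (assumed) | 1.033 | 5.8% |
| 6.2 | implied by 95 per arm | 1.063 | 6.5% |
| 7.3 | 95 over 13 sites, one cluster each (assumed) | 1.076 | 6.9% |
| 8 | full group as one cluster (assumed) | 1.084 | 7.1% |
| 11.6 | 151 over 13 sites, one cluster each, no attrition (assumed) | 1.125 | 8.1% |

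**4. Range over the ICC, at m = 6.2.** ICC 0: 5.0%. ICC 0.01: 5.3%. ICC 0.02: 5.6%. ICC 0.05: 6.5%. ICC 0.10, a value not in the article: 8.1%.

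**5. Simulation of the model as written.** Patient and site random intercepts, arm-by-visit effects, visits at 3, 6, 9 and 12 months, complete data, assumed within-patient correlation 0.5, 8,000 runs per setting, critical value 1.96. The Monte Carlo standard error near 7% is √(0.07 × 0.93/8000) ≈ 0.3 points.

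| Clusters per site, ICC 0.05 | 95 per arm | 151 per arm |
|---|---|---|
| one | 7.1–7.3% | 8.6–8.7% |
| two | 6.0–6.2% | 6.9–7.0% |
| three | 5.8% | 5.9–6.2% |

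At ICC 0 the same model gave 4.7% to 5.9%, so a few tenths of a point of any single entry may be unrelated to clustering. The simulation agrees with the formula in direction and approximate size, and shows that the site intercept does not remove the effect.

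**6. Power with the clinician effect in the model.** At 95 per arm and m = 6.2, SE = 20 × √(2.26/95) = 3.085. Then 10/3.085 − 1.96 = 1.28, which is 90.0% power by the normal approximation.

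**The case against.** The strongest reply is that the article speaks only of potential clustering and an assumed correlation. It offers no evidence that the ICC is above zero, and at zero the model as written is sound. That stands. A reader might infer that the primary test is certain to exceed 5%; the documents support only the conditional statement that it would do so if the clustering the plan assumes is present.

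A second reply concerns size. A reader might take 7% or more as the headline, on the footing of one therapy group per site. The article gives neither the number of groups per site nor the number of participants per clinician. It places the ICC at clinician level and puts two clinicians on each group, which points to smaller clusters. Clustering by group is a reasonable inference from the description of delivery, but rolling entry means members overlap only in part, and the plan assigns no correlation to groups. This also stands, and it is why the figure at the plan's implied cluster size leads here.

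A third reply is that the SAP, to be agreed before unblinding, may already contain the term. It may. That would settle the analysis, but the article's explicit list of random effects would then need correcting to match.

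A reader might also extend the point to the secondary outcomes. The article names no random effects for those models, so it contains no misstatement to correct there.

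**Conclusion.** The inconsistency is real, and its effect is modest. Under the plan's own ICC of 0.05 and the 6.2 participants per clinician that its sample size implies, the 12-month standard error is about 6% too small and two-sided type I error is about 6.5%. Depending on the unstated cluster size, it lies between about 5.8% and 8%; the simulated 8.6–8.7% arises only with one cluster per site and no attrition at all. If the ICC is zero there is no excess.

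These figures rest on the assumed ICC, equal cluster sizes, a normal critical value and, in the simulation, complete data with a within-patient correlation of 0.5.

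The sample size is not at fault: it reproduces, and it already allows for the correct analysis. The point still deserves correction because it concerns the confirmatory test of a trial that describes itself as definitive, and a standard error that is too small makes a false positive more likely.

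**What to change.** Add to the primary model a random effect for allocated clinician that applies in the MBT arm only (a random coefficient on the MBT indicator, by clinician), and keep the patient and site effects. Therapy group could serve instead if membership is recorded; the article confirms an allocated clinician but does not say that a group identifier is kept. Where a site has a single cluster, the term amounts to a random site-by-treatment effect.

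Use a small-sample degrees-of-freedom method such as Kenward-Roger: at 6.2 per clinician, 95 analysed MBT participants come from only about 15 clinicians (95/6.2).

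State the term in the SAP and bring the article's primary outcome paragraph into line with it before unblinding. If the SAP already has it, only the article needs correcting.

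The cost is one variance component and slightly wider intervals, by about 6% at ICC 0.05 and a little more from the degrees-of-freedom method, which would also take power slightly below the normal-approximation 90%. The target of 302 stays as it is. Arm-specific residual variance, and a matching term in the secondary models, are options for the SAP and not part of this defect.

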#### Secondary outcomes

For the secondary outcomes, we will use mixed-effects linear regression for continuous outcomes, mixed-effects logistic regression models for binary outcomes, and mixed-effects Poisson models for count data such as number of offences. Missing outcome data due to dropout will be accounted for by the mixed-effects model under a missing-at-random assumption; missing covariates will be accounted for using multiple imputation.

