#### Objective measures

Objective outcomes of health service use will be collected from record linkage using participants’ NHS numbers at 6-monthly intervals during the intervention and the follow-up period until the 24-month follow-up point.

Objective outcomes of offending behaviour, including withdrawal of licence, arrests, and reconvictions, will be collected from police computer records at 6-monthly intervals, for the 6 months before randomization and during the intervention and follow-up period until the 24-month follow-up point. The number of records of offending behaviour (count data) will be obtained, and 6-month periods free of any offending behaviour will also be recorded (binary data). Data will be obtained from participants’ records on nDelius (the national public sector offender case-management system) and the Police National Computer database; these records detail information on breaches of licence conditions, police contacts, charges, court appearances, criminal orders, arrest rates, and frequency, severity, and type (violent/non-violent) of offending behaviour.

These objective outcomes of health service use and offending behaviour will be available regardless of loss to follow-up; this will allow the use of multiple imputation techniques. If loss to follow-up is considerably different between arms and the primary outcome is significant, we will perform a sensitivity analysis to the impact of missing data not being missing at random, as described by White et al. [80].

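### The mixed-effects Poisson model for offence counts has no term for extra variation within a 6-month period, so period-by-period treatment tests would be liberal

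*Protocol article*

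**What the plan says.** The article's Statistical analysis section, under Secondary outcomes, assigns "mixed-effects Poisson models for count data such as number of offences". It names no dispersion parameter, observation-level effect, negative binomial alternative or robust variance. It also does not list the random effects or the treatment contrast for counts. For the primary outcome the article does state both: "Patient ID and site will be included as random effects", with a separate treatment effect at every follow-up time and the 12-month one of main interest.

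Under Objective measures, the outcome is described this way: "The number of records of offending behaviour (count data) will be obtained". The data "will be collected from police computer records at 6-monthly intervals", which gives 24 / 6 = 4 periods after randomization. On content, "these records detail information on breaches of licence conditions, police contacts, charges, court appearances, criminal orders, arrest rates", followed by the frequency, severity and type of offending. A companion binary outcome marks 6-month periods without offending.

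**The concern.** Given its random effects, a Poisson model takes the variance of a count to equal its mean. Two features of these data work against that.

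- **Batching.** One incident can plausibly lead to an arrest, a charge, a court appearance and an order. If records are summed, they arrive in clumps.
- **Changing rates.** The Randomization section foresees recall to prison and new custodial sentences, and the Discussion gives recall as the reason for 35% of dropouts so far. A man's rate is unlikely to be constant across four periods.

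A patient intercept is one constant per man, so it cannot represent either feature inside a given period. Standard errors for a period-specific treatment effect then come out too small.

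The stakes are moderate. Offending is among the domains the investigators call key. Record-based outcomes (offending and health service use) "will be available regardless of loss to follow-up", which matters in a trial expecting 37% attrition. The Moderators section also carries any secondary outcome found significantly different on to interaction testing, so a false positive would be followed up.

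**Working it through.** **The plan's own figures.** The article gives no number for the count analysis. Its sample size, used below, reproduces: 95 / (1 − 0.37) = 150.8, rounded up to 151 per arm, and 2 × 151 = 302.

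**How large the extra variance can be.** Let a man have N incidents in a period, Poisson with mean λ, and let incident j generate R_j records. With Y = ΣR_j, the mean is λE[R] and the variance is λE[R²], so variance / mean = E[R²] / E[R]. The Poisson model fixes this at 1.

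| Records per incident (assumed) | E[R] | E[R²] | Variance / mean |
|---|---|---|---|
| 1 | 1 | 1 | 1 |
| exactly 2 | 2 | 4 | 2.0 |
| 1 + Poisson(1) | 2 | 1 + 4 = 5 | 2.5 |
| 1 + Poisson(2) | 3 | 2 + 9 = 11 | 3.7 |

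**Where it bites.** For an effect averaged over periods, the relevant noise is how men's totals differ. The estimated intercept variance captures that, batching included. For one period, the model allows the intercept variance plus Poisson noise, while the data carry Poisson noise multiplied by the ratio above. The relative shortfall is greatest when men otherwise differ little.

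**Simulation.** No treatment effect, 302 men allocated 1:1, four periods, two-sided 5%, 500 runs per row. The Monte Carlo standard error near 5% is √(0.05 × 0.95 / 500) = 1.0 point. Models were fitted by maximum likelihood with fine-grid integration. Runs with coarse 41-point quadrature were inaccurate for large counts and were dropped. Incidents per period, records per incident and the SD of men's log rates are all assumptions.

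Type I error, %. Columns A to D are Poisson models; E estimates the variance of the log rate ratio from the data.

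- A: patient intercept, effect averaged over periods
- B: patient intercept, one effect per period, 12-month period tested
- C: 12-month period analysed alone, patient-level intercept
- D: 24-month total, site intercept only
- E: empirical variance, 12-month period

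| Incidents | Log-rate SD | Records per incident | A | B | C | D | E |
|---|---|---|---|---|---|---|---|
| 1 | 1 | 1 | 4.8 | 4.0 | 5.2 | 50.6 | 5.0 |
| 1 | 1 | 2 | 4.2 | 6.4 | 4.6 | 63.0 | 5.0 |
| 1 | 1 | 1 + Poisson(1) | 5.0 | 7.8 | 4.6 | 62.2 | 5.8 |
| 1 | 1 | 1 + Poisson(2) | 4.4 | 9.2 | 5.4 | 71.0 | 6.2 |
| 0.4 | 1 | 1 + Poisson(2) | 4.8 | 9.2 | 4.6 | 58.6 | 5.0 |
| 1 | 0.5 | 1 + Poisson(2) | 6.2 | 14.0 | 3.4 | 48.2 | 4.4 |
| 1 | 0 | 1 + Poisson(2) | 4.4 | 18.2 | 5.6 | 28.6 | 4.8 |

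The 24-month total with a patient-level intercept gave the same rates as column A. The smallest inflated value in B, 6.4%, is only 1.4 Monte Carlo standard errors above 5%; the others are clearer.

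**Rates that also vary within a man.** In further runs with 0.4 incidents per period and log-rate SD 1, the per-period error was about 8.5% with batching and 14% when rates also varied within man. A mixed-effects negative binomial model on the same data gave about 3% to 5%. Runs with gamma-distributed rates gave 9% to 11% with batching alone and 10% to 15% with within-man variation added. In those runs the averaged effect was about 4% to 9%, so its near-nominal behaviour is good but not perfect.

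**In terms of interval width.** If the test statistic is roughly normal, the true standard error is 1.96 / z times the reported one, where z is the two-sided normal point for the actual error rate. At 6.4% this is 1.96 / 1.85 = 1.06; at 9.2%, 1.96 / 1.685 = 1.16; at 18.2%, 1.96 / 1.335 = 1.47.

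**The case against.** The strongest reply is that the model is mixed-effects, and a patient random effect is itself a standard device for overdispersion. This stands for the averaged effect and for a single count per man, where columns A and C show no inflation. It does not stand for per-period tests.

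Second, the per-period contrast and the patient and site effects are stated only for the primary outcome, and the analysis plan, which is not shown, may settle both for counts. This also stands: their absence is no fault, and the point is conditional on that contrast. The Poisson distribution, however, is a choice the article makes.

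Third, batching is an inference. Objective measures names licence withdrawal, arrests and reconvictions as the outcomes, the longer list describes what the databases hold, and the analysis section speaks of offences. No sentence says that linked records are added together. But the section does define the count as a number of records, so the inference is fair.

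A reader might go further and infer that the planned analysis produces false positives in general, or at the very high rates of column D. The article does not support this. No section specifies a model without a patient-level term. Column D is also 50.6% with one record per incident, so it mostly reflects differences between men, not batching.

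**Conclusion.** The point holds in a limited form. If offence counts are compared period by period with a patient intercept as the only patient-level term, and records are batched or rates drift within men, type I error is about 6% to 18% instead of 5%. With large stable differences between men (log-rate SD 1) and batching alone, the main simulation gives 6.4% to 9.2%. The 14.0% and 18.2% values need small or no differences between men, although within-man rate variation brings the SD 1 case to about 14% as well. The article gives no figures for incident rates, records per incident or rate variation, so the direction is firmer than the size.

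The averaged effect, a single count with a patient-level intercept, and the binary offence-free outcome are not materially affected. The primary outcome is not involved. The change is worth making because the remedy is cheap and better calibrated, and because significant secondary outcomes go on to moderator testing.

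**What to change.** In the Statistical analysis section, under Secondary outcomes, and in the analysis plan:

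1. For count outcomes, replace the mixed-effects Poisson model with a mixed-effects negative binomial model with patient and site effects, or keep Poisson and use patient-clustered robust standard errors. The negative binomial gave about 3% to 5% in the scenarios tested. A data-estimated variance gave 4.4% to 6.2% for the 12-month period across the batched scenarios.
2. Where the records allow, count distinct offences or incidents, not every linked record.
3. Confirm that a patient-level effect is in the count model, and say whether treatment is tested per period or averaged.

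The first and third changes need only wording and a different model call. The second needs a way to link records from one incident, such as an offence date, which the article does not list; hence the condition. The price is wider intervals for per-period count comparisons, by roughly 6% to 16% in the batching-only scenarios with log-rate SD 1 and more where the extra variation is larger. That is the width needed for correct coverage. Follow-up was still in progress at the time of the article, which says the analysis plan will be agreed before the statistician sees unblinded data, so the change can be made there.
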